## Abstract

**Background:** Heart failure (HF) is one of the major causes of mortality worldwide, representing the terminal stage of several cardiovascular diseases. Exercise-based rehabilitation is a beneficial therapy for patients with chronic heart failure (CHF). However, there is a lack of specific guidance on clinical decision-making regarding optimal exercise intensity. It is necessary to optimize the clinical recommendations for HF exercises. We will evaluate the efficacy and safety of different aerobic exercise intensities in patients with heart failure with reduced ejection fraction (HFrEF): the HF-EI trial. This trial aims to assess the appropriate exercise intensity for patients with HFrEF.

**Methods:** After a baseline assessment to determine the safety of exercise, 180 patients will be randomly assigned to supervised high-intensity exercise training (ET) group, supervised moderate intensity training (MIT) group, and control group at a ratio of 1:1:1. Patients randomly receiving high intensity training (HIT) undergo supervised ET (3 times/week, 30 min) for aerobic endurance at 70% peak oxygen consumption (peak VO_2_) intensity for 12 weeks. The MIT patients will perform supervised aerobic ET (3 times/week, 35–42 min) at the anaerobic threshold (AT) intensity for 12 weeks. The control group will continue to maintain their daily activities and will not receive ET. During the baseline and follow-up period, physical examination, laboratory tests, cardiology diagnostic tests, cardiopulmonary exercise tests (CPET), 6-min walk distance (6MWD), scale scores, exercise steps, medications, and clinical events will be monitored. Throughout the research, sport bracelets and patient diaries will be used to monitor and record overall physical activity, training courses, and compliance.

**Discussion:** The HF-EI trial will evaluate the effects of different aerobic exercise intensities on peak VO_2_, quality of life (QoL), and clinical events among patients with HFrEF. The findings of this trial will provide a basis for formulating exercise prescriptions for patients with HFrEF.

**Clinical Trial Registration:**http://www.chictr.org.cn/, identifier: ChiCTR2000036381.

## Introduction

Chronic heart failure (CHF) is a severe and end-stage manifestation of several cardiovascular diseases. It is a syndrome with a high hospitalization rate, high disability rate, and high mortality rate, causing an economic and social burden on families (1). According to statistics, there are 64.3 million heart failure (HF) patients worldwide. In developed countries, the prevalence of adult HF is 1–2% (2). The China Hypertension Survey (CHS) showed that 1.3% of Chinese people aged ≥35 years, or an estimated 13.7 million individuals had HF (3). At present, there are many treatment option [s]s for HF, including general therapy, medication, and non-drug treatment (4). Despite active exploration of new medical and non-drug treatments for HF, the final effect is still unsatisfactory. The challenges facing HF intervention include optimizing HF treatment and reducing overall costs associated with long-term management.

Exercise training (ET) is a safe and effective treatment for HF. As shown in previous randomized controlled trials, it can significantly improve exercise capacity and quality of life (QoL) (5). Furthermore, ET is associated with reductions in mortality and hospitalization and recommended in the current guidelines on CHF management (6).

A massive amount of evidence suggests that ET is beneficial for patients with HF (7–16). A study by Belardinelli et al. in 2012 showed that exercise rehabilitation for up to 10 years could significantly reduce the readmission rate and the risk of cardiovascular death (17). A Cochrane review in 2019 found that exercise-based cardiac rehabilitation (CR) may have little effect on short-term all-cause mortality but may improve long-term all-cause mortality (>12 months follow up).CR probably reduces overall hospitalization rates in the short term (6).

However, data from the Exercise Training Meta-Analysis of Trials in Chronic Heart Failure (ExTraMATCH) II trial with at least 3 weeks of ET in HF showed that exercise-based CR had no significant effect on the risk of mortality and hospitalization in heart failure with reduced ejection fraction (HFrEF) (18).

Studies on the effects of exercise-based CR on the mortality and hospitalization rate of patients with HF show conflicting results, possibly attributed to differences in exercise pattern, exercise intensity, patient population selection, compliance, and follow-up time. All factors, especially exercise intensity, may affect the endpoint effect. Therefore, further research is needed to determine optimal exercise intensity to reduce the mortality and HF hospitalization rate.

Since the 1980s, numerous studies have demonstrated the safety and effectiveness of moderate intensity training (MIT) (19, 20). However, recent data suggest that high intensity training (HIT) may offer some advantages over MIT (21–32). Within a specific intensity range, exercise intensity is proportional to the effect. However, higher exercise intensity is associated with higher risk, and a higher need for adjusted to ensure safety and effectiveness in patients with HF. The mainstream sports rehabilitation model in developed countries of Europe and the United States is based on rehabilitation centers and ET under electrocardiogram (ECG) monitoring. A 12-week, three times a week treadmill exercise is used as a classic exercise prescription (33). The advantage is that it considers the efficacy and safety of ET, providing tremendous benefits to patients with HF in the short term. Keteyian et al. found that a moderate amount of exercise (3–7 metabolic equivalent hours per week) in patients with HF reduces the risk of clinical events, and within this range, an increase in the amount of exercise is associated with increased benefits (34). Swank et al. also obtained similar results. After exercise rehabilitation in patients with HF, increased peak oxygen consumption (peak VO_2_) was associated with improved prognosis (35).

According to the grading standards for exercise intensity proposed by the 2020 European Society of Cardiology (ESC) Guidelines on sports cardiology and exercise in patients with cardiovascular disease, the anaerobic threshold (AT) intensity is moderate, 70% PeakVO_2_ intensity is high intensity (36). We will design a three-arm randomized controlled experiment to explore the effectiveness and safety of moderate exercise intensity (AT intensity) in the treatment of HFrEF. The HIT (70% PeakVO_2_ intensity) group served as the active control group, and the daily activity group served as the placebo control group. Mainly compare MIT and HIT, or MIT and daily activities, and explore the dose-effect relationship of exercise intensity on changes in clinical outcomes through regression analysis. We assume that MIT has a greater impact in the main results than HIT and daily activities.

We will evaluate the efficacy and safety of different aerobic exercise intensities in patients with HFrEF: the HF-EI trial. This study is the first multicenter randomized controlled trial (RCT) on the effects of different aerobic exercise intensities in patients with HFrEF in China. By collecting data on exercise capacity and exercise rehabilitation, we will evaluate the clinical efficacy of exercise-based CR in Chinese patients with HFrEF. Finally, suitable exercise intensity will be recommended for the popularized HFrEF aerobic exercise program for Chinese patients with HFrEF.

The primary objective of the HF-EI trial is to investigate the effects of different exercise intensities on exercise capacity and quality of life in patients with HFrEF. As secondary objectives, the HF-EI trial will evaluate AT oxygen uptake, 6-min walk distance (6MWD), left ventricle ejection fraction (LVEF), N-terminal prohormone of brain natriuretic peptide (NT pro-BNP), the Patient Health Questionnaire-9 (PHQ-9), General Anxiety Disorder-7(GAD-7), all-cause mortality, HF hospitalization, major cardiovascular events, and adverse events.

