### Outcome Measures

The primary outcome for the HF-EI trial is the change in peak VO_2_ and Minnesota Living with Heart Failure Questionnaire scores (MLHFQ)after 12 weeks. We choose the common primary outcomes in order to obtain the comprehensive effect of different exercise intensities on HFrEF treatment. Aerobic exercise has a well-known positive effect on patients with HFrEF in exercise capacity and quality of life, and peakVO_2_ is an important indicator for evaluating the prognosis of HF (22, 40).

Secondary outcomes included, AT oxygen uptake, 6MWD, LVEF, NT pro-BNP, PHQ-9, GAD-7, all-cause- mortality, hospitalization events for HF, major cardiovascular events, and adverse events.

The test indicators require patients to be measured at the hospital rehabilitation center. The test details are as follows:

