### Statistical Methods

The calculation of the sample size will be based on the primary outcome of the RCT. The sample size calculation was performed using PASS V11.0 (NCSS Company of the United States) with the following calculation formula:

$$\begin{array}{l} n=\Psi^{2}\left[\sum_{i=1}^{k}s_{i}^{2}/k\right]/\left[\sum_{i=1}^{k}{\left({\bar{X}}_{i}-\bar{X}\right)}^{2}/\left(k-1\right)\right]\left(k\;=\;3\right) \end{array}$$

The parameters are set to double-sided α = 0.05, β = 0.1, Power = 1–β = 90%, the average difference in peak VO_2_ of the three groups were 0, 2, 4(ml/kg/min) and the average difference in MLHFQ of the three groups were 2, 12, 10. The corresponding standard difference values of peakVO_2_ were 6, 4, 6 (ml/kg/min) and MLHFQ were 5, 18, 16.

The parameter estimation is based on the results of previous researches (22, 42, 43).

A total of 180 cases were required for the three groups, 60 patients in each group, considering the 20% loss to follow-up rate and stratification factors. Because each of the primary endpoints can be individually reflected in clinical significance. Therefore, if one of the two primary endpoints of the intervention group improves significantly, the study is successful.

Blinded statistical analysis will be performed by qualified statisticians using PASW Statistics 18.0 (IBM SPSS Inc., Armonk, New York, USA). The measurement data will be expressed as mean ± standard deviation (x ± s), measurement data by *t* test, and count data by chi-square test. The clinical events of the treatment groups will be statistically compared, according to the principle of intention-to-treat. The Kaplan–Meier method will be used to calculate the cumulative event rate. The event time of all patients will be measured starting from the randomization time (time zero). We will collect all available information on clinical events until the last patient contact, including patients who withdraw consent or those lost to follow-up. Relative risk (RR) will be calculated using the Cox proportional hazard model. If a sufficient number of events occur, the Kaplan–Meier curve will be used for stratified analysis of the exercise group, and the log-rank test will be used to test the difference in survival. The significance level will be set at *p* < 0.05.

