AT relates to the point when the exercise load increases to a certain amount and the tissue demand for oxygen exceeds the amount that the circulation can provide, and the tissues undergo anaerobic metabolism to provide more energy. The critical point from aerobic metabolism to anaerobic metabolism is called AT, expressed as the threshold oxygen consumption of anaerobic metabolism (VO_2_ AT), equivalent to 50–60% of peak oxygen consumption, and directly detected by CPET (44). The advantages of using AT as the basis for formulating exercise prescriptions are sub-maximal exercise intensity, which can prevent the continuous increase of lactic acid levels, avoid hyperventilation and shortness of breath, avoid metabolic alkalosis, reduce the occurrence of overload on the heart and arrhythmia, and ensure high safety. Aerobic exercise with the intensity of the AT has protective effects on CHF, confirmed by the literature (45). For patients with HFrEF, exercise intensity is a range, not a point; AT belongs to sub-maximum medium intensity. Although 70% of peakVO_2_ is high- intensity, it is not ultra-high intensity. This study will explore the effects of these two different intensities.

AT intensity has not been widely accepted internationally. This study compares the effectiveness and safety of AT intensity and high intensity in patients with HF, and aims to reflect the superiority of AT intensity exercise. It has reference value for other colleagues in the world.

Limitations of the study should be recognized as follows: lost to follow-up, influencing factors including patient age, difficulties attending appointments, concurrent illnesses, and the nature of the intervention that made blinding impossible. We made every effort to ensure that evaluators, laboratory technicians and statisticians remain unaware of the treatment allocation.

Altogether, the results of the HF-EI trial may provide evidence on the effective delivery of a contextually adapted exercise-based CR program in China. At the same time, it provides evidence of AT exercise intensity for the world's CR field.

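### The sample-size means, read in one arm order, do not assume that MIT leads on both primary outcomes, and the 90% power does not extend to MIT versus HIT

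*Protocol article*

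**What the plan says.** The Introduction sets out the comparisons, "Mainly compare MIT and HIT, or MIT and daily activities", and then the expected result: "We assume that MIT has a greater impact in the main results than HIT and daily activities". The Discussion adds that the study "aims to reflect the superiority of AT intensity exercise", AT being the MIT intensity.

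Outcome Measures names two primary outcomes: "The primary outcome for the HF-EI trial is the change in peak VO_2_ and Minnesota Living with Heart Failure Questionnaire scores (MLHFQ)after 12 weeks".

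Statistical Methods gives a three-group sample-size formula and these inputs:
- Error rates: "The parameters are set to double-sided α = 0.05, β = 0.1, Power = 1–β = 90" (per cent).
- Peak VO2 means: "the average difference in peak VO_2_ of the three groups were 0, 2, 4(ml/kg/min").
- MLHFQ means: "the average difference in MLHFQ of the three groups were 2, 12, 10".
- Standard deviations: "The corresponding standard difference values of peakVO_2_ were 6, 4, 6 (ml/kg/min) and MLHFQ were 5, 18, 16".

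No value is tied to a named arm. The result is 60 per arm and 180 in total after allowing for 20% loss. A significant improvement on either primary outcome counts as success.

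**The concern.** The hypothesis ranks MIT first. The largest planned peak VO2 value is third in its list and the largest MLHFQ value is second in its list, so one arm cannot hold both if the order is common. The expectation printed in the Introduction and the numbers behind the sample size then describe different results.

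This matters because the Introduction promises that a suitable intensity will be recommended. If the two primary outcomes point in opposite directions for MIT versus HIT, as the planning values suggest, the trial can meet its either-endpoint rule and still give no basis for preferring one intensity. A direction declared in advance also invites a reader to lean on whichever outcome agrees with it. A reader may further take the 90% power to cover MIT versus HIT, the first comparison named.

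**Working it through.** **1. Reproducing the plan's own figure.** Inputs are from Statistical Methods: k = 3, two-sided alpha 0.05, power 90%, 20% loss.

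- Peak VO2: mean variance (36 + 16 + 36)/3 = 29.33. Grand mean 2, so between-group variance (4 + 0 + 4)/2 = 4. Solving with the noncentral F gives n = 48 per arm (power 0.904), and 48/0.8 = 60.
- MLHFQ: mean variance (25 + 324 + 256)/3 = 201.67. Grand mean 8, so between-group variance (36 + 16 + 4)/2 = 28. This gives n = 47, and 47/0.8 = 58.75, rounded up to 59.

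The larger value, 60 per arm, gives the stated 180. Relabelling the arms does not change it.

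**2. Direction under every labelling.** Both lists are taken in one arm order, with MLHFQ values read as improvements.

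| Order of arms | MIT − HIT, peak VO2 | MIT − HIT, MLHFQ | MIT leads both? |
|---|---|---|---|
| Control, MIT, HIT | −2 | +2 | No: HIT ahead on peak VO2 |
| Control, HIT, MIT | +2 | −2 | No: HIT ahead on MLHFQ |
| HIT, control, MIT | +4 | +8 | No: control ahead of MIT on MLHFQ (12 vs 10) |
| HIT, MIT, control | +2 | +10 | No: control ahead of MIT on peak VO2 (4 vs 2) |
| MIT, control, HIT | −4 | −8 | No: MIT lowest on both |
| MIT, HIT, control | −2 | −10 | No: MIT lowest on both |

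MIT leads both in 0 of 6. Reading MLHFQ as a signed change with lower values better does not help: the best value, 2, is then in position 1, which has the lowest peak VO2 value.

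**3. What the F test's power rests on, with control first.** Each between-group sum of squares splits into control versus the mean of the exercise arms, and MIT versus HIT.

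- Peak VO2: total 8. Control versus exercise is (3 − 0)² × 2/3 = 6; MIT versus HIT is 2²/2 = 2.
- MLHFQ: total 56. Control versus exercise is (11 − 2)² × 2/3 = 54; MIT versus HIT is 2²/2 = 2.

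MIT versus HIT thus supplies a quarter of the signal on peak VO2 and 2/56 (under 4%) on MLHFQ.

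**4. Power for MIT versus HIT, with control first.** Evaluable per arm: 60 × 0.8 = 48. Power is approximately Φ(d/SE − 1.96).

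- Peak VO2: d = 2, SDs 4 and 6, SE = √(52/48) = 1.041. Power = Φ(1.92 − 1.96) ≈ 48%.
- MLHFQ: d = 2, SDs 18 and 16, SE = √(580/48) = 3.476. Power = Φ(0.575 − 1.96) ≈ 8%.

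With no loss at all (60 per arm) these become 57% and 9%. For 90% power, n per arm = (1.960 + 1.282)² × (sum of the two variances)/d²: 10.51 × 52/4 ≈ 137 for peak VO2 and 10.51 × 580/4 ≈ 1,524 for MLHFQ.

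Under control, MIT, HIT these are the chances of finding HIT better on peak VO2 and MIT better on MLHFQ. Under control, HIT, MIT the directions swap and the sizes stay the same.

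**The case against.** The strongest reply is that the plan claims less than this. The formal primary objective is neutral: it investigates the effects of different intensities. The hypothesis speaks of the main results together, not of each outcome. One primary outcome suffices for success, and with control first MIT is planned ahead of control on both outcomes and ahead of HIT on one. The superiority phrase is Discussion prose, not a test. The values come from earlier studies that may not share an arm order, and where the article lists its arms it puts HIT first and control last. The Introduction also notes that higher intensity carries higher risk, which is its reason for studying MIT.

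Much of this stands, and it rules out three stronger readings that a reader might infer:
- That the inputs favour HIT over MIT on one outcome under every labelling. They do not: with HIT first, MIT is ahead of HIT on both. Those orders instead put control ahead of MIT on one outcome, which still conflicts with the hypothesis.
- That MIT superiority on both outcomes is impossible. Planning means are assumptions and do not limit what the data can show.
- That 180 is wrong. It reproduces exactly.

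The conflict between the printed hypothesis and the printed inputs remains, as does the gap between the 90% and the first-named comparison. Neither is a detail left to an analysis plan, since the hypothesis, the inputs and the success rule all appear in this article.

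**Conclusion.** The point holds as an inconsistency between hypothesis and planning values, not as an error in the sample size. In any common arm order the planning means do not give MIT the lead on both primary outcomes. With control first, HIT is planned 2 ml/kg/min better on peak VO2 or 2 points better on MLHFQ. The 90% power belongs to the overall three-group test. At the plan's own inputs MIT versus HIT has about 48% power on peak VO2 and 8% on MLHFQ.

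The conclusion rests on three readings that the article does not state: both lists share one arm order, MLHFQ values are improvements, and control is first. The first is essential. If the lists were in different orders, MIT could lead both. The second does not affect the finding that MIT never leads both. The third fixes which outcome favours HIT and the power figures.

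**What to change.** - Label each planning mean and SD by arm, state the sign convention for MLHFQ, and reconcile the values with the hypothesis in the Introduction and the aim in the Discussion.
- State that the 90% power applies to the overall three-group test, and give the MIT versus HIT power for each primary outcome.
- Keep MIT versus HIT as a main comparison, but report it as a two-sided difference with a 95% CI on both primary outcomes and no presumed direction.
- State that neither meeting the either-endpoint rule nor opposite directions on the two outcomes will by itself support a claim that one intensity is superior.

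The cost is a change of wording and a more modest claim. No extra patients are needed and the trial's question stays as it is. Restricting confirmation to exercise versus control is not needed for this fix and would change that question.

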## Methods/Design

### Design

This will be a multi-center, parallel, three-group RCT to evaluate the efficacy and safety of MIT for HFrEF. Eligible participants will be randomly assigned to the HIT intervention group receiving a 12-week supervised training sessions (70% PeakVO_2_ intensity) plus usual medications, MIT intervention group receiving a 12-week supervised training sessions (AT intensity) plus usual medications, or a control group receiving only the usual medication and maintain daily activity. This study has a 12-week intervention and a 12-month follow-up period. Figure 1 shows the study design flow chart. This protocol follows the Standard Protocol Items: Recommendations for Interventional Trials (SPIRIT) guidelines and fulfills the SPIRIT checklist (Supplemental File 1); A SPIRIT checklist is provided in Figure 2 (37).

**Figure 1 F1:**
[figure not shown]
Flow chart of the study. RCT, randomised controlled trial; HIT, high intensity training; MIT, moderate intensity training.

**Figure 2 F2:**
[figure not shown]
Standard protocol items. Peak VO_2_, peak oxygen consumption; NT-proBNP, N-terminal prohormone of brain natriuretic peptide; PHQ-9, Patient Health Questionnaire-9;GAD-7, General Anxiety Disorder-7.

### Setting and Participants

The HF-EI trial aims to recruit 180 stable HFrEF patients in three study sites (Tongji Hospital Affiliated to Tongji University, Yueyang Integrated Traditional Chinese Medicine and Western Medicine Hospital Affiliated to Shanghai University of Traditional Chinese Medicine, and Longhua Hospital Affiliated to Shanghai University of Traditional Chinese Medicine) in China and apply standard therapy in accordance with the ESC HF guidelines. We have predefined a set of inclusion and exclusion criteria (Table 1) to ensure the feasibility and safety of ET. The main method of recruiting patients is to screen the patients on-site when visiting a doctor.

**Table 1 T1:** HF-EI trial inclusion and exclusion criteria.

**Inclusion criteria**
1. Aged 18 to 75 years old
2. BMI 18–30 kg/m^2^
3. LVEF <0.4
4. NYHA I-III.
5. Clinical symptoms are stable for at least 2 weeks
6. The dose of angiotensin-converting enzyme inhibitor/angiotensin receptor antagonist/angiotensin receptor enkephinase inhibitor, beta-blocker, aldosterone inhibitor and other drugs was stabilized for at least 2 weeks.
7. Written informed consent.
